## **12. Time schedule of enrolment and assessment**

Recruitment into the trial will commence in January 2022 and will continue for 24 months. Final assessments (T5) are expected to be completed by 31 March 2025. The enrolment and group allocation are shown in Figure 1. The overall trial duration is 39 months. This is from first participant enrolled to the last follow-up assessment of the final participant is completed. Each individual participant will remain in the trial for approximately 12 months.

## **13. Sample size**

A total of 352 parents and their children will be recruited into the study. This power calculation is based on projected effects at the primary endpoint (3 months post-randomisation). As behaviour problems measured with the ODD subscale of the SNAP-IV questionnaire (Swanson et al., 2001) is our primary outcome, we estimated the smallest difference of clinical importance between STEPS and WAU to be equivalent to an effect size  $d = 0.4$  standard deviations based on the NICE guidance supporting the use of PT for the treatment of ODD or conduct disorder (Lundahl, Risser, & Lovejoy, 2006). A within trial drop-out rate of 25% is assumed. This is higher than in most previous trials of face-to-face PT programmes because of the unsupported nature of STEPS in OPTIMA. We will monitor drop-out rates during the internal pilot and, if necessary, recalculate the sample size if it is higher than the 25% estimated. Using Stata (version 14.0) command *sampsi*, ANCOVA analysis with a conservative zero correlation assumed between baseline and primary endpoint SNAP-IV ODD score, a two-sided test and an alpha of 0.05, we estimated that 176 individuals will be needed per trial arm (total n = 352) to provide 90% power to test the hypothesis that STEPS is superior to WAU.

[figure not shown]

Figure 1. OPTIMA enrolment, group allocation and follow-up flowchart.

## 14. Recruitment

### 14.1 Method 1: myHealthE portal

In some of the participating organisations, clinical triage and rapid screening for high levels of hyperactivity/impulsivity, inattention, and conduct problems will occur as part of routine care using myHealthE (MHE) - a Caldicott Guardian approved, General Data Protection Regulation (GDPR) compliant, online portal for the automated screening of referred families using NHS CAMHS data (Ibrahim et al., 2015). MHE uses a secure text/email system through which primary caregivers are invited to register and complete validated clinical screening measures using an online portal. These are then automatically coded using standard algorithms to subsequently allow the research team to identify potentially eligible parents. MHE also seeks parents' permission to be contacted with invitations to take part in research studies; that is, provide consent-for-contact. By consenting to research contact, parents also give their permission for Trust-approved researchers to review their children's medical records to establish eligibility.

Authorised staff will regularly input the new referrals' details into MHE, which will initiate the mechanism for obtaining the initial consent for research contact and for obtaining the screening information. Research assistants will regularly log in to the MHE researcher portal (this portal only includes information about children whose parents gave consent-for-contact) to check for any new cases flagged up as 'eligible'. All

researchers conducting these reviews will have an appropriate letter of access or equivalent authorisation from the participating organisation, will be GCP trained, appropriately experienced, and have been delegated this responsibility by the CI on the delegation log. Research assistants will identify potential participants by reviewing cases flagged up as 'eligible' by MHE using a standard algorithm. To be flagged as 'eligible' the case must fulfil the following criteria: (1) a child is aged 5 years 0 months to 11 years 11 months, (2) a child screened positive for high levels of hyperactivity/impulsivity, inattention, and conduct problems on the SDQ; (3) a child is not under local authority care; and (4) a parent provided routine consent for research contact. The 'eligible' flag will be treated as a potential participating family.

In first instance, researchers will contact parents of eligible children by email with an invitation to take part in the study and a Parent Information Sheet. Non-responders will be followed up by phone, text message or post. If a parent expresses an interest in taking part (verbally, by email or by returning an expression of interest form), a researcher will arrange an initial telephone appointment with a parent to explain the details of the study, assess their English language competence and ascertain they have access to a STEPS compatible digital device. Assuming both the language screen and the device screen are positive parents will be asked to complete the consent form for the study online. There will be a minimum of 5 days between an invitation to take part and the initial telephone appointment.

#### **14.2 Method 2: Interactive CAMHS Assessment Network (ICAN)**

In North East London NHS Foundation Trust, routine outcome measures are collected through the Interactive CAMHS Assessment Network (ICAN). It is a digital application in which clinicians, young people, parents, caregivers, and teachers can provide routine clinical measures. ICAN provides useful feedback to clinicians to help track progress and data in real-time and is directly linked to the electronic patient record.

Parents of newly accepted referrals, who provide consent for research contact through ICAN, will be asked to complete the SDQ also through ICAN. This information will be then passed onto the research team, who will review the SDQ scores to establish eligibility. Parents of children who meet eligibility criteria will be approached by the researcher with an invitation to take part (by email, phone or post). Once a parent expresses an interest in taking part, a researcher will arrange a phone call to take the parent through the study details and the rest of the procedure will be identical to that described for participants identified through MHE (see 'Method 1: myHealthE portal').

#### **14.3 Method 3: Manual review of current referrals**

Manual review will be used if neither of digital methods (i.e., MHE or ICAN) are available within the participating organisation, or in case of any technical difficulties affecting the use of a digital platform.

##### **14.3.1 Consent for contact**

Members of the clinical teams in the participating organisations ask parents of patients if they are happy to be contacted about any relevant research. If they answer yes, this is recorded in their electronic health record

and gives Trust-employed Clinical Study Officers (CSOs) or researchers permission to screen their record for suitability and then make direct contact with the parent to invite them to the study.

The details of parents, who meet eligibility criteria and have given consent for contact will be securely transferred via encrypted email to the research team. Parents will be approached by the researcher with an invitation to take part (by email, phone, or post). Once a parent expresses an interest in taking part by responding to the invitation (by email, phone, or post), a researcher will arrange a phone call to take the parent through the study details and the rest of the procedure will be identical to that described for participants identified through MHE (see 'Method 1: myHealthE portal').

#### **14.3.2 Clinic referral**

Members of the clinical teams in the participating organisations will specifically discuss the study with the parent during a routine clinical contact and if they are interested and give verbal permission then pass their details to CSOs or researchers to take forward from there. This will act as their referral into the study.

Information about the study, including a link to access the online information sheet, may also be emailed or posted by the clinical team to families (see 'Invitation letter/email wording'). Additionally, trust employed CSOs can be co-opted to work alongside the clinical team and make the initial contact with the parent (by phone) to invite them to take part in the study. The details of parents, who expressed interest in taking part in the trial will then be passed to the members of the research team via encrypted email and parents will be approached with an invitation to take part, as described above.

#### **14.4 Clinician interviews recruitment**

Clinicians taking part in the qualitative interviews (n ~ 10; see 11. Process evaluation) will be recruited from the services involved in the study. Service managers will be approached with a request to circulate the Clinician Information Sheet to the members of the team and the clinicians interested in taking part will be asked to contact the research team directly.

### **15. Allocation**

Once the parent is enrolled in the study (i.e., after eligibility criteria are confirmed and informed consent has been obtained) and has completed the baseline assessments, they will be randomised to either the STEPS or WAU. Randomisation will be carried out online via a [randomisation platform](#) provided by Sealed Envelope in a 1:1 ratio and stratification by trial centre location (London, Nottingham, Southampton) using random permuted blocks procedure with varying block sizes. The researcher designated by CI (the trial manager or the trial administrator) will access the randomisation service, complete an on-screen form with participant details, inclusion and exclusion criteria and the randomisation allocation will be released. Randomisation system will use a unique identifying number. The web-based database system will send an automatic email confirmation of randomisation to unblinded researchers, who performed randomisation. The parent will be notified of the treatment allocation electronically (via email) or by phone by the researcher, who performed randomisation.

## **16. Blinding**

Parents taking part in the study will remain unblinded throughout the trial; they will be informed about their group allocation after randomisation. Every effort will be taken to ensure that research assistants remain blinded (e.g., they will not have access to the app usage data). In addition, the risk of unblinding the research assistants will be minimal, as all follow-up data will be collected online using Red Pill Electronic Patient Outcome Forms (ePRO). The same number of automatic email/text prompts to complete the study measures will be sent to each participant, regardless of their arm allocation. To minimise the risk associated with unblinding during qualitative interviews, research assistants will conduct interviews with parents recruited from outside their local trial centre.

The senior statistician and senior health economist will not have access to the randomisation list or ePRO forms at any point in the trial to remain fully blinded until review of the first draft of the statistical/health economic reports for checking, when they will become fully unblinded. Similarly, the Chief Investigator and Principal Investigators in each trial centre will remain fully blinded until they review the finalised statistical report, when they will become fully unblinded. The junior statistician and junior health economist will be partially blinded until sign off of the statistical and health economic analysis plans, after which they will be fully unblinded so they can inspect and utilise app usage/therapy-related data. The trial manager and the trial administrators will be unblinded. The only individuals that will be able to summarise/see data by arm prior to the review of the statistical report are the junior statistician, junior health economist and the members of the data monitoring committee. We will presume that the data monitoring committee will remain partially blinded and will prepare the closed report accordingly. No serious harms associated with taking part in the intervention are expected, therefore a formal procedure for unblinding any blinded staff during the study is not needed.

## **17. Data collection**

All OPTIMA trial data will be collected remotely: online, by phone and via video/audio chat. For each participant, assessments will take place over the period of 12 months and will be conducted at five timepoints as described above [baseline (T1), T2, T3, T4, T5]. The assessment window will cover a period of six weeks and will begin two weeks before the scheduled assessment and will close four weeks after the scheduled assessment. As a thank you for taking part, parents will receive shopping vouchers: £10 at baseline, £25 voucher at T2 and £10 voucher after completing T3, T4 and T5 assessments. Children will receive a £5 book voucher and a certificate for each completed task. The vouchers will be emailed to participants.

Four categories of data will be collected in the study: (1) participants' reports on the outcome measures and information about adverse events; (2) a speech sample audio-recorded during a remote parent-child drawing task (ESO); (3) the STEPS app usage data (for the intervention group only) and (3) video and audio recordings of qualitative interviews.

- (1) Outcome data and information about adverse events will be collected online using [Red Pill](#) – a secure electronic data capture and management system provided by Sealed Envelope or over the phone by a trained researcher.

In first instance, participants will be notified by email and/or a text message when a scheduled assessment requires them to complete the questionnaires online using subject entered forms (ePRO) system provided by Red Pill. They will be able to complete the questionnaires using the browser on their computer or phone. Researchers will be able to track questionnaire completion within Red Pill using a display listing both complete and incomplete questionnaires for each participant. Up to three emails/text messages will be sent as reminders to complete online forms. Non-responders will be followed up with phone calls until the end of the assessment window. Through the information sheet, participants will be informed that, if they wish, they can also complete the questionnaires or provide information about adverse events over the phone. If they opt to provide information over the phone, a research assistant will arrange a convenient time to speak to the participant and will enter data onto either a paper form and later transfer the data into the study data base or directly onto an electronic form within Red Pill database during a phone call with a participant. Data entered into the Red Pill database will be de-identified.

- (2) A 5-minute speech sample will be recorded during an online parent-child interaction drawing task via Microsoft Teams (ESO). During the task, participants will be identified by their unique ID number. They will also be asked to turn their camera off. The recorded sample will be rated by a trained researcher using Child Oppositional and Defiance Speech Sample Scale (CODSS) and observer's rating scores will be entered onto an electronic form within the Red Pill database.
- (3) All app usage data will be collected within Google Firebase and will be stored with Google servers. Usage data held within Google Firebase will be of non-identifiable nature and will be stored against the study ID. Therefore, the risk of harm to participants following a potential privacy breach is low. Access to the STEPS Google Firebase account will be restricted to authorised users in the research team and external staff responsible for the app maintenance and support.
- (4) Video and audio files. Whenever possible remote interviews will be conducted and recorded via Microsoft Teams. In case it is not possible to conduct an interview via Teams, participants will be given an option to take part in a telephone interview, which will also be recorded with Microsoft Teams. During remote interviews (via Microsoft Teams or telephone) participants will be identified by their unique ID number. Alternatively, a researcher will email a participant a list of questions, and they will be asked to respond by providing responses in text form. For interviews conducted by email, participants will be advised that security cannot be guaranteed when communicating by email using a non-secure email address and that it is not possible to maintain anonymity during data collection, but that any identifying information (e.g., their name and email address) will be redacted from the text and their de-identified data will be stored using a study ID.

## **18. Data management**

### **18.1 Study database**

The main trial database for the study will be provided by Sealed Envelope, which will ensure there are robust processes for quality management, security and back up of data <https://www.sealedenvelope.com/security/>. Database services and support and electronic data capture will be delivered through a service level agreement between Sealed Envelope and KCL. Access to the database and electronic data capture forms will be restricted by user identifiers and passwords to a limited number of researchers (i.e., trial manager and trial administrator, junior statistician, research assistants). Blinded researchers will not be able to view randomisation information within the database.

Sealed Envelope uses [Red Pill](#)- an online application for collecting and managing case report form (CRF) data on participants recruited to a clinical trial or other research studies. In this study, Red Pill will be used to record data collected offline (e.g., phone or medical records) as well as collect data directly from parents themselves [electronic patient reported outcomes (ePRO)].

The system used in the OPTIMA trial will be specifically configured for the study.

### **18.2 Data storage and data transfer**

Handling of all data collected in the OPTIMA trial is described in detail in the OPTIMA Data Management Plan. In brief:

Data held within Red Pill database: Extracts of data will be downloaded by a junior trial statistician in plain text comma separated value format (.csv files) or Stata fixed format with a dictionary. Data will be retained within Red Pill database for three months after the database lock. After this time, all data files will be downloaded and stored within KCL SharePoint site and the Red Pill database will be deleted.

STEPS usage data: Extracts of the app usage data will be downloaded by researchers in plain text comma separated value format (.csv files). After data collection has been completed, all usage data will be downloaded onto KCL SharePoint site. The app-related Google Firebase account and all the data contained within the STEPS account will be deleted after the analysis is completed and the results are published in a peer-review journal.

Audio recordings of the speech sample during the ESO task recorded via Microsoft Teams will be initially stored within Microsoft Stream and access to Stream will be restricted by user identifiers and passwords. After a session, audio recordings will be downloaded onto a KCL OneDrive for Business and the files will be deleted from Microsoft Stream. The original recordings will be deleted from OneDrive for Business after transcription and coding have been completed.

Qualitative interviews: Consent forms completed by clinicians will be downloaded from Qualtrics and stored in electronic form on a KCL OneDrive for Business and SharePoint location, which is a web-based, Microsoft Office integrated collaborative platform. Video and audio recordings from the qualitative

interviews recorded via Microsoft Teams will be initially stored within Microsoft Stream and access to Stream will be restricted by user identifiers and passwords. Video and audio recordings and automatically generated transcripts will be downloaded onto a KCL OneDrive for Business and the files will be deleted from Microsoft Stream. The automatically generated transcripts will be checked by the members of the research team against the original recording and edited to remove any identifiable information. Interviews provided via email responses will be downloaded onto a KCL OneDrive for Business and de-identified. All de-identified transcripts and email responses will be stored in electronic form on a KCL OneDrive for Business and SharePoint location. The original recordings or emails will be deleted from OneDrive for Business after transcription.

Paper forms: Paper forms will be stored in the locked cabinet in the Trial Manager's office located in the Department of Child & Adolescent Psychiatry at King's College London.

Only de-identified data files will be used for analyses. The data extracted from the Red Pill database, the STEPS app usage data and qualitative interviews data will be linked using the study ID. All data files will be stored on King's College SharePoint location for the period of 7 years. The data stored on SharePoint are encrypted and access to the data will be restricted only to those who need to have it. All databases will be registered in the King's Data Protection Register (KDPR). After 7 years, personal data will be securely destroyed, and fully anonymised research data will be transferred to King's College Research Data Management or other suitable repository for long-term storage and stored for 13 years (overall, data will be held for 20 years).

## 19. Statistical analysis

### 19.1 *Clinical effectiveness*

**Does STEPS reduce the average levels of *parent-rated* child behaviour problems in children screened positive for high levels of hyperactivity/impulsivity, inattention, and conduct problems, measured over a three- (primary outcome and timepoint), six-, nine- and 12-month (secondary outcomes) period, when compared to Wait-As-Usual (WAU)?**

**Does STEPS reduce the average levels of parent-rated child hyperactivity/impulsivity and inattention screened measured over a three- and 12-month (secondary outcomes) period, when compared to WAU?**

**Does STEPS improve the average levels of: parenting style, satisfaction and efficacy, and child-parent closeness; and reduce parental strain (additional secondary outcomes) in parents of children screened positive for high levels of hyperactivity/impulsivity, inattention, and conduct problems, measured over a three- and 12-month period, when compared to WAU?**

**EXPLORATORY 1: Does STEPS reduce the average level of children's oppositional and defiant speech measured by CODSS during an online child-parent interaction task (ESO) at 3- and 12-months post-randomisation, as compared to WAU?**

**EXPLORATORY 2: Does STEPS reduce the average level of children's emotional problems measured at 3- and 12- months post-randomisation, as compared to WAU?**

**EXPLORATORY 3: Does STEPS reduce the reduces the likelihood of a clinical diagnosis being made and medication prescribed by the 12 months follow up, as compared to WAU?**

The main analysis will follow the intention to treat (ITT) principle as much as possible (Sullivan et al., 2018; White et al., 2012). A mixed effects linear analysis of covariance (ANCOVA) model with repeated measures will be used with the SNAP-IV ODD scores at three (primary outcome), six, nine and 12 months (secondary outcomes) post-randomisation as the dependent variables, and intervention group, time point, intervention group by time point interaction, baseline SNAP-IV ODD score, and the trial centre stratification variable as independent variables, with the interaction term used to extract the primary and secondary outcome STEPS vs WAU mean differences and associated 95% confidence intervals at the four time points. Similar statistical models will be used to test for intervention effects on the other continuous secondary and exploratory outcome scale scores (average levels of directly observer-rated child behaviour problems (ESO), parent-rated hyperactivity/impulsivity and inattention, parenting style, satisfaction and efficacy, child-parent closeness and parenting-related strain) with the scores extracted at the timepoints listed in section 10 'Measures and outcomes'. For the binary exploratory diagnosis and medication outcomes we will use modified Poisson regression with robust standard errors to estimate STEPS vs WAU relative risks (and associated 95% confidence intervals) for getting a diagnosis and being prescribed medication (Zou, 2004).

In addition to ITT analysis, we will undertake a complier average causal effect (CACE) sensitivity analysis (Angrist, Imbens, & Rubin, 1996; Dunn et al., 2015) on the ODD outcome primary outcome at 3 months (T2) and ODD secondary outcome at 12 months (T5), to estimate treatment effects in those who completed at least two modules of the STEPS app (i.e., those that complied with the intervention).

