### **5.2 Secondary objectives**

1. To test for the maintenance of effects observed regarding primary outcome at 6-, 9- and 12-months post-randomisation.
2. To test whether STEPS reduces the severity of parent-rated hyperactivity/impulsivity and inattention at 3- and 12-month follow-up, as compared to WAU.
3. To test whether STEPS improves parenting (i.e., style, satisfaction, and efficacy), increases child-parent closeness and reduces parenting-related strain at 3- and 12-month follow-up, as compared to WAU.
4. To establish the cost-effectiveness of STEPS compared to WAU at 3- and 12-months post-randomisation with outcomes measured in terms of quality adjusted life years.
5. To use qualitative data from parents and clinicians to explore: how STEPS works; what the mechanisms of change are; and contextual factors influencing implementation of the app, in a way that is consistent with MRC guidelines for complex intervention process research.

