## 6. Study design

A two-arm superiority parallel randomised controlled trial with an internal pilot study (see below), with measures taken at baseline (T1), scheduled within one month before randomisation and then at three months (T2 primary outcome, primary timepoint), six months (T3), nine months (T4) and 12 months (T5) post-randomisation.

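### One baseline ODD slope serves all four follow-ups in the primary model; adding baseline by time point is a nearly free safeguard, mainly for the 12-month maintenance estimate

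*Protocol*

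**What the plan says.** Protocol section 6 sets the follow-ups at "three months (T2 primary outcome, primary timepoint), six months (T3), nine months (T4) and 12 months (T5) post-randomisation". Section 19.1 fits one mixed model to all four ODD scores, with "intervention group, time point, intervention group by time point interaction, baseline SNAP-IV ODD score, and the trial centre stratification variable as independent variables". From it the plan takes the STEPS minus WAU "mean differences and associated 95% confidence intervals at the four time points". Baseline ODD appears as a main effect only, and the one time interaction listed is with intervention. Models of the same kind are planned for the other continuous outcomes, most of which are measured only at 3 and 12 months.

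The later contrasts answer secondary objective 1 in section 5.2: "To test for the maintenance of effects observed regarding primary outcome at 6-, 9- and 12-months post-randomisation". Section 13 plans with d = 0.4 SD, "a two-sided test and an alpha of 0.05", and a zero correlation between baseline and 3-month ODD. It gives no correlation for 6, 9 or 12 months. Section 19.2 leaves further detail to a statistical analysis plan that is not at hand.

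**The concern.** A single baseline slope is a compromise across visits. If baseline ODD predicts the 3-month score more strongly than the 12-month score, the fitted slope lies between the two: too shallow at 3 months and too steep at 12. This alone does no harm in a randomised comparison. It matters when the participants observed in the two arms also differ in mean baseline ODD, because part of that difference is then left in the 3-month contrast and too much of it is removed at 12 months.

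Parts of the protocol make each condition plausible without showing it. Section 9.4 expects no assessment or treatment before 3 months but allows access to services over the full 12, which could weaken the link between baseline and later scores. Section 13 attributes its drop-out assumption to the unsupported nature of STEPS, and section 9.4 gives WAU families the app only after their 12-month follow-up, so the incentive to stay may differ by arm. What is at stake is chiefly the 12-month maintenance estimate.

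**Working it through.** **1. The plan's own sample size.** n per arm = 2(z₀.₉₇₅ + z₀.₉₀)²/d² = 2(1.960 + 1.282)²/0.4² = 131.3, so 132. Dividing by 1 − 0.25 gives 132/0.75 = 176 per arm, 352 in total, as stated. Power with 132 completers per arm is 0.901. The calculation takes no credit for baseline adjustment.

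**2. Size of the shift.** Let β_t be the true baseline slope at visit t, b the fitted common slope, and Δ_t the STEPS minus WAU gap in baseline ODD among those observed at t. Then

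shift at t (common slope minus visit-specific slopes) ≈ (β_t − b) × Δ_t.

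Lower ODD is better, so a negative shift favours STEPS. Either factor being zero removes the shift.

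Example (assumed slopes 0.65, 0.55, 0.45, 0.35; gap 0.199 SD; no missing data). With unstructured covariance the fitted b was 0.558:
- 3 months: (0.65 − 0.558) × 0.199 = +0.018 (model fit: +0.016)
- 12 months: (0.35 − 0.558) × 0.199 = −0.041 (model fit: −0.041)

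Here b lies above the plain average of 0.50, nearer the 3-month slope, which is why the 3-month error is the smaller one.

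**3. Large-sample scenarios.** None of these inputs is in the protocol. Outcome SD is 1 and slopes fall from 0.60 to 0.45, 0.65 to 0.35, or 0.70 to 0.30. Where data are missing, the proportion rises from 25% at 3 months to 40% at 12.

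| Scenario | Gap, 3 / 12 months | Shift at 3 months | Shift at 12 months |
|---|---|---|---|
| Drop-out related to baseline alike in both arms, unstructured | about 0 | 0.000 | at most 0.001 in size |
| Fixed gap, no missing data, unstructured | 0.20 / 0.20 | +0.011 to +0.016 | −0.016 to −0.063 |
| Drop-out opposite by arm, unstructured | −0.25 / −0.38 | −0.012 to −0.018 | +0.030 to +0.115 |
| Same, compound symmetry | −0.25 / −0.38 | −0.015 to −0.043 | +0.028 to +0.087 |

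A separate fit with completer gaps of 0.09 to 0.20 SD gave −0.004 to −0.017 at 3 months and +0.009 to +0.032 at 12. Runs with slopes 0.65, 0.50, 0.45, 0.40 and baseline-related drop-out in STEPS only gave −0.017 and −0.031 at 3 months, and +0.014 and +0.026 at 12, for a moderate and a strong gradient. The −0.031 is the largest 3-month shift seen with unstructured covariance at gaps up to 0.25 SD. Doubling the gradient in the opposite-drop-out scenario roughly doubles the gaps and the shifts.

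**4. At the trial's size** (N = 352, true effect −0.4 SD, 500 replicates, drop-out opposite by arm, gaps −0.24 / −0.37 SD, unstructured covariance):

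| Slopes | Visit | Bias, common slope | Bias, with interaction | Difference |
|---|---|---|---|---|
| 0.65 to 0.35 | 3 months | −0.019 | −0.002 | −0.018 |
| 0.65 to 0.35 | 12 months | +0.072 | −0.013 | +0.085 |
| 0.60 to 0.45 | 3 months | −0.015 | −0.002 | −0.013 |
| 0.60 to 0.45 | 12 months | +0.025 | −0.012 | +0.038 |

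(Differences are taken before rounding.) The standard error is about 0.10 at 3 months and 0.12 to 0.13 at 12. For slopes 0.65 to 0.35, 95% interval coverage is 92.8% against 93.0% with the interaction at 3 months, and 90.6% against 94.2% at 12 months. Power is 98.8% against 98.2%, and 73% against 90%. For slopes 0.60 to 0.45, 12-month power is 86% against 92%. Simulation error is about 0.13/√500 = 0.006 on a 12-month bias and √(0.94 × 0.06/500) = 0.011 on a coverage, so the paired differences are firmer than any single bias, and the 3-month coverages do not differ. With drop-out alike in both arms the two models agree within 0.003 SD.

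**5. Chance imbalance alone.** With 132 completers per arm the baseline gap has standard deviation √(2/132) = 0.123. A slope error near 0.1 gives a usual 3-month shift of about 0.1 × 0.123 ≈ 0.01 SD.

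**The case against.** The listed model is a legitimate repeated-measures ANCOVA. Randomisation makes the expected baseline gap zero unless drop-out is differential, and section 19.2 defers detail to a plan that could add the term. No slope is given for any visit beyond the planning value of zero at 3 months, and nothing shows that drop-out will depend on baseline ODD differently by arm. Sections 16 and 25.4 send both arms the same number of prompts and keep inviting parents who stop using the app. All of this stands, and it makes the point conditional and minor. It does not remove it: section 19.1 does list the terms, and an analysis plan that follows them would carry the constraint forward.

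A reader might infer more than the protocol supports:
- **That the primary result is distorted.** The 3-month shift is small against its standard error, and coverage and power there are practically unchanged.
- **That completers differing from drop-outs is enough.** It is not; the gap must be between the arms.
- **That the sample size is undermined.** Section 13 assumes zero correlation, so 176 per arm stands whichever slope is fitted.
- **That the opposite shifts at 3 and 12 months should be added together.** Section 19.1 extracts a difference at each visit and plans no contrast between visits.
- **That centre also needs a time interaction.** No calculation here supports that.

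**Conclusion.** The point holds as a minor, conditional one. It requires a baseline slope that declines over time and a baseline ODD gap between the arms' observed participants; both are assumptions. For the primary 3-month estimate the effect is about 0.00 to 0.02 SD with unstructured covariance (0.03 in one set of runs, up to 0.04 with compound symmetry), which would not alter the reading of a 0.4 SD effect. For the 12-month estimate it is about 0.01 to 0.03 SD with completer gaps of 0.1 to 0.2 SD and moderate slope decline. It reaches about 0.06 SD for a 0.2 SD gap with the steepest decline tried, and about 0.1 SD when steep decline is combined with opposite drop-out by arm. With flat slopes or drop-out alike in both arms it is essentially nil.

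**What to change.** In section 19.1, add a baseline SNAP-IV ODD by time point interaction to the primary model. In the models for the other continuous outcomes measured at 3 and 12 months, add that outcome's baseline by time point. If the statistical analysis plan already contains these terms, bring the protocol text into line with it.

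The cost is three extra parameters in the ODD model, with about 352 × 0.75 = 264 participants expected at 3 months, and one in each two-timepoint model. The sample size stays at 352, and no data collection or design feature changes. Centre can stay as a main effect.
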